## Abstract

**Background:**

African American adults experience a disproportionate burden and increased mortality for most solid tumor cancers and their adolescent children are negatively impacted by the illness experience. The purpose of this randomized clinical trial is to evaluate the efficacy of a culturally sensitive family-based intervention program developed for African American families coping with solid tumor parental cancer using an intention-to-treat approach. Primary outcome is adolescent depressive symptoms at end of treatment.

**Methods:**

A sample of 172 African American families will be enrolled from two diverse oncology centers (Helen Graham Cancer Center in Newark, DE, and Kimmel Cancer Center in Philadelphia, PA). Eligible families will be randomized either to a 5-session intervention Families Fighting Cancer Together (FFCT) or a 5-session parent-only psycho-educational (PED) program. Assessments will occur at weeks 0 (baseline), 8 (end-of-treatment), 24, and 52.

**Discussion:**

Treatments to help African American adolescents cope with the impact of parental cancer are scarce and urgently needed. If successful, this proposed research will change the nature of intervention support options available to African Americans, who are overrepresented and underserved by existing services or programs.

**Trial registration:**

This project is registered with ClinicalTrials.gov (Protocol #: NCT03567330).

## Background

In 2018, an estimated 1.7 million newly adult cancer cases will be diagnosed in the United States [1]. Breast cancer, lung, prostate and colorectal cancer are among some of the most common cancer cases projected in 2018 [2]. Of these 1.7 million adults new diagnosed with cancer in 2018, nearly 800,000 children 18 years old or younger will be affected by a parent’s cancer diagnosis [2]. Moreover, three million children under the age of 18 face the devastating challenge of coping with a parent who is living with cancer [2]. Parental cancer is associated with significant emotional distress in both diagnosed parents and their children [3–5]. In addition, many parents diagnosed with cancer experience high rates of depressed mood for two or more years post their initial diagnosis [6, 7]. In some cases, parents with cancer have an absence of depressed mood, although in most incidences parents diagnosed with parental cancer face treatment demands and preoccupation with cancer. This can lead to these parents with cancer more likely to be physically and emotionally unavailable to their children in the home [5, 8–10]. Consequently, these children whose parents have cancer, an estimated 22–33% of these children are more likely to display clinical levels of emotional distress, particularly adolescents (ages 12–18) [11, 12].

African American adults experience a disproportionate burden for most solid tumor cancers (e.g., breast, prostate, colorectal, lung) and have higher cancer mortality rates than Whites [13]. African American women have a higher incidence of breast cancer and higher rates of mortality under the age of 50, when these women are more likely to be raising children [14]. Collectively, African American men and women have a higher incidence of colon cancer, while African American men have a higher incidence of prostate cancer at all ages [13, 15]. These facts raise concern for the African American children of these diagnosed parents with cancer being at a high risk for parental cancer-related distress. African Americans have not been well represented in intervention studies compared with White middle-class samples [16]. Despite the known burden of parental cancer on adolescents, the substantial under-representation of African Americans in the clinical trial literature, and the dominance of studies with primarily White parents and children, there have been no randomized clinical trial intervention studies to assist African American parents and their adolescents navigate the illness burden of the parent’s cancer. Prior research suggests African American patients tend not to volunteer for clinical trials because of understandable mistrust of providers and a perceived lack of cultural sensitivity and institutional as well as structural barriers to recruitment and participation [15–18]. Adaptations tailored to a specific ethnic/racial group are more effective than those adapted for a variety of minority groups [19]. Additionally, differences in attitudes, daily functioning, and levels of distress among different ethnic and racial groups are well-documented [18–22]. Many African Americans face stressors which can influence and exacerbate difficulty in coping with cancer, such as but not limited to: financial challenges, community violence, substandard educational system, single-parent households, racial discrimination, heath treatment disparities, urban blight, etc. [18–22] Thus, taking these barriers into consideration, this 5-session 8-week culturally sensitive intervention, African American Families Fight Cancer Together (FFCT) will be compared with Psychoeducation (PED).

Two theoretical frameworks were selected to support the direction of this research trial. Each attachment theory and social learning theory provide the theoretical foundation of the Families Fighting Cancer Together (FFCT) intervention model [23, 24]. Investigators in this research also borrowed perspectives regarding the treatment structure and content from Beardslee’s work with families coping with parental depression and Clarke’s work preventing depression and anxiety in adolescents [25, 26].

## Aims

### Primary aim

Aim 1. Compare the efficacy of FFCT to PED in reducing depressive symptoms among African American (AA) adolescents at post-treatment using an intention-to-treat (ITT) analysis.

### Secondary aim

Aim 2. Compare the efficacy of FFCT to PED in reducing parental stress among AA parents at post-treatment using ITT analysis.

### Exploratory aims

Aim 3a. Determine treatment differences in trajectories of adolescent depressive symptoms, adolescent anxiety, and parental stress from baseline to 12-month follow-up.

Aim 3b. Determine whether perceived levels of group support, adolescent gender and age, parent’s marital and socioeconomic status, and parent’s cancer staging modify the effects of treatment on adolescent depression and anxiety.

Aim 3c. Determine whether pre-post changes in parent-adolescent attachment and communication mediate the association between treatment and adolescent depressive symptoms and anxiety at 6- and 12-month follow-ups.

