#### Study measures/assessments

This study uses valid and reliable measures, all of which were used in our most recent pilot study with AA families, where there was no evidence or report of respondent burden or fatigue. The assessment schedule appears in Table 1.

**Table 1 Tab1:** Assessment Schedule

	*Source*	*Wk 0*	*Wk 8*	*Wk 24*	*Wk 52*
*General and Program Descriptive*					
*Demographic Family Survey*	*Parent*	*∙*			
*Consumer Satisfaction*	*Adol/Parent*		*∙*		
*Adolescent Psychological Outcomes*					
*Child Depression Inventory (CDI-2)*	*Adol*	*∙*	*∙*	*∙*	*∙*
*Revised Child Manifest Anxiety Scale (RCMAS-2)*	*Adol*	*∙*	*∙*	*∙*	*∙*
*Parent Psychological Outcomes*	*Parent*	*∙*	*∙*	*∙*	*∙*
*State-Trait Anxiety Inventory (STAI)*	*Parent*	*∙*	*∙*	*∙*	*∙*
*Center Epidemiological Depression Scale (CES-D)*	*Parent*	*∙*	*∙*	*∙*	*∙*
*The Functional Assessment of Cancer Therapy FACT-G (version 4)*	*Parent*	*∙*	*∙*	*∙*	*∙*
*Parent-Adolescent Relational Outcomes*					
*Security Scale*	*Adol*	*∙*	*∙*	*∙*	*∙*
*Short Form Interaction Behavior Questionnaire (IBQ)*	*Adol/Parent*	*∙*	*∙*	*∙*	*∙*
*General Communication*	*Adol/Parent*	*∙*	*∙*	*∙*	*∙*
*Treatment Moderators*					
*Parenting Concerns Questionnaire (PCQ)*	*Parent*	*∙*	*∙*	*∙*	*∙*
*Helpful Group Experiences (HGE)*	*Parent*		*∙*		

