#### Perceived level of group support

The *Helpful Group Experiences (HGE)* is a 17-item adapted valid and reliable measure that assesses the helpfulness of experiences in a support group [48, 49]. The HGE includes 5, four point-subscales, including altruism (e.g., “I offered empathy or compassion”), cognitive growth, and informational (e.g., gained access to important information) support (e.g., got support and encouragement). The HGE will be used only at post-intervention (week 8) to assess parents’ perceptions of group experiences. The 5 subscales have acceptable internal consistency ranging from α = .71–.93 [49].

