#### Exploratory aim 3b

Determine whether perceived group support, adolescent gender and age, parent’s marital and socioeconomic status, and parent’s cancer staging modify the effects of treatment on child depression and anxiety. We will extend the models estimated above to evaluate key theoretically derived interaction terms. Predicted values will be plotted and, where appropriate, effect modifiers will be dichotomized to capture the region of effect modification. We will estimate standard errors and confidence intervals using bootstrap replications when indicated. Prior research with predominantly white samples suggests the intervention will reduce child depression and anxiety and parental stress to a greater extent for parents perceiving more group support, parents who are single and of low socioeconomic status, adolescent girls, older adolescents, and parents with more severe stages of solid tumor cancer.

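### Exploratory Aim 3b tests perceived group support as an effect modifier, but it is rated only at week 8, after randomisation, so its interaction with treatment does not estimate effect modification

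*Protocol article*

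**What the plan says.** - **Exploratory aims, Aim 3b:** "Determine whether perceived levels of group support, adolescent gender and age", together with marital status, socioeconomic status and cancer stage, modify the effect of treatment on adolescent depression and anxiety. Group support stands in one list with five characteristics that exist before randomisation.
- **Analysis plan, Exploratory aim 3b:** "We will extend the models estimated above to evaluate key theoretically derived interaction terms". The predicted direction is a larger benefit "to a greater extent for parents perceiving more group support". After predicted values are plotted, "where appropriate, effect modifiers will be dichotomized to capture the region of effect modification".
- **Perceived level of group support:** the instrument is the HGE, which "assesses the helpfulness of experiences in a support group". On timing: "The HGE will be used only at post-intervention (week 8) to assess" parents' perceptions.
- **Table 1:** the row "Helpful Group Experiences (HGE)" stands under the heading for treatment moderators, with the parent as source and a single mark.
- **Randomization** and **Abstract, Methods:** allocation follows the baseline assessment, and week 8 is the end of treatment and the primary endpoint visit.
- **Exploratory aim 3c:** the mediation analysis covers attachment and communication only. HGE is given no process, within-arm or principal-stratum role anywhere in the article.

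**The concern.** A moderator analysis keeps the protection of randomisation only if the moderator is fixed before allocation. The arms are then balanced within each level of the moderator, and a difference between levels is a difference in treatment effect. HGE fails this condition. It rates the group that the family was allocated to, and the groups differ by design: FFCT has one parent session and two multi-family sessions after two adolescent sessions, while PED is parent-only education. An FFCT parent with a high HGE and a PED parent with a high HGE are not exchangeable. For week-8 outcomes, the modifier is also collected at the same visit as the outcome.

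At stake is a misread exploratory result. The protocol predicts more benefit with more perceived support. If HGE follows outcome more closely in FFCT than in PED, a constant treatment effect produces an interaction with exactly that sign, and the artefact would read as confirmation.

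**Working it through.** **1. The plan's own figure.** Inputs from the section Statistical power: d = 0.38, pre-post correlation r = 0.68, α = .05 (taken as two-sided), power .8, retention 70%.

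- Residual variance after ANCOVA: 1 - 0.68² = 0.5376, so the residual SD is 0.733.
- n per arm = 2 × (1.960 + 0.842)² × 0.5376 / 0.38² = 58.5, rounded up to 59. At 60 per arm the power is 0.81.
- 120 / 0.70 = 171.4, rounded up to 172.

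The stated 60 per arm and 172 reproduce. The protocol gives no figure for Aim 3b, so the rest uses this design.

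**2. A model with no true moderation.** Post = 0.68 × Pre - 0.38 × FFCT + 0.733 × e. The effect is -0.38 SD for every family. HGE has within-arm SD 1, is 0.5 SD higher in FFCT (assumed), and has correlation c₀ (PED) or c₁ (FFCT) with -e, that is, with a better outcome than the baseline score predicts. The values of c₀ and c₁ are assumptions.

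**3. What the interaction model then estimates**, with HGE centred at its overall mean:

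- Interaction = -0.733 × (c₁ - c₀)
- Its standard error ≈ 0.733 × √[(2 - c₀² - c₁²) / 60]
- Treatment coefficient at average HGE = -0.38 + 0.25 × 0.733 × (c₀ + c₁). The 0.25 appears because each arm's HGE mean lies half of 0.5 SD from the overall mean.

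Worked case, c₀ = 0 and c₁ = 0.4: interaction = -0.733 × 0.4 = -0.293. Standard error = 0.733 × √(1.84 / 60) = 0.128. The ratio is 2.28, so the rejection rate at nominal 5% is about P(Z > 1.96 - 2.28) ≈ 0.63. Treatment coefficient = -0.38 + 0.25 × 0.733 × 0.4 = -0.31.

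**4. Results** (the last column is from 4,000 simulated trials per row):

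| c₀ (PED) | c₁ (FFCT) | Interaction (true value 0) | Treatment coefficient at average HGE (true value -0.38) | False interaction rate, formula | False interaction rate, simulated |
|---|---|---|---|---|---|
| 0 | 0 | 0 | -0.38 | 5% | 5% |
| 0.2 | 0.2 | 0 | -0.31 | 5% | 5% |
| 0.3 | 0.3 | 0 | -0.27 | 5% | 5% |
| 0.4 | 0.4 | 0 | -0.23 | 5% | 4% |
| 0.1 | 0.2 | -0.07 | -0.32 | 9% | 8% |
| 0.3 | 0.4 | -0.07 | -0.25 | 9% | 9% |
| 0.2 | 0.4 | -0.15 | -0.27 | 21% | 20% |
| 0 | 0.2 | -0.15 | -0.34 | 20% | 19% |
| 0 | 0.3 | -0.22 | -0.33 | 39% | 38% |
| 0 | 0.4 | -0.29 | -0.31 | 63% | 60% |

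**5. A second mechanism.** HGE was also made to depend on an unmeasured prognostic factor that has correlation 0.5 with the outcome residual. At a total of 120, the false interaction rate was 12% to 50% when the dependence was stronger in FFCT, and 5.2% when it was equal. In the same data sets a pre-randomisation modifier gave 4.4% to 5.8%, which is the nominal level. The excess therefore comes from using a post-randomisation modifier and not from the interaction test.

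**The case against.** The strongest reply concerns size. The high rates need HGE to be unrelated to outcome in PED. It is tempting to justify that by saying that PED adolescents attend no group, but HGE is completed by parents, and PED parents attend a facilitated group for all five sessions. If HGE tracks outcome equally in both arms, the interaction test keeps its 5%. HGE and the CDI also come from different informants, parent and adolescent, so a story in which families who did well simply rate their group higher is not established. All of this stands. It turns the size into a range that starts near 5%. It does not rescue the estimand: even with equal correlations, the treatment coefficient in the HGE model moves away from -0.38.

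The aim is exploratory, and the other five modifiers are baseline characteristics. In models extended to weeks 24 and 52, HGE precedes those outcomes, so they cannot have influenced it. That also stands, but HGE remains post-randomisation.

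Two stronger readings are not supported:

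- **That a false result would decide who is offered FFCT.** HGE does not exist until the group has been attended, so it cannot select families beforehand.
- **That the plan tests cut-points chosen from the data.** The wording, "effect modifiers will be dichotomized to capture the region of effect modification", comes after the interaction terms and the plots, and may only describe an interaction already tested. It is ambiguous and is not a demonstrated error.

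**Conclusion.** The point holds in a limited form. A parent rating of the assigned group, taken only at week 8, is not a valid effect modifier, and the article states both its timing and its role without a safeguard. Under a constant effect of -0.38 SD with 60 per arm, the false interaction rate runs from about 5% (equal tracking in both arms) through 8-20% (modestly unequal) to about 60% (0.4 in FFCT, zero in PED). With equal correlations of 0.2 to 0.4 and an assumed 0.5 SD shift in HGE, the treatment coefficient at average HGE lies between -0.31 and -0.23.

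The correlations and the shift are assumptions, so a reader should not infer that a false finding is likely at any particular rate. Nor does the point reach Aims 1 and 2, the sample size or the remaining Aim 3b modifiers. It is a correction worth making to one part of one exploratory aim.

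**What to change.** - Remove perceived group support from the modifiers in Aim 3b and from its directional hypothesis, and move HGE out of the moderator heading in Table 1.
- Restrict the modifiers to variables recorded at baseline.
- Report HGE as a process variable: the between-arm difference at week 8 and the within-arm associations with outcome, labelled non-causal. Moving it into the mediation analysis would not remove post-treatment confounding and would need that caveat.
- As a secondary clarification, state that interactions with continuous modifiers are tested with the modifier kept continuous, and that any dichotomisation is for display only.

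The cost is wording and a small change of analysis, with no new data or visits. The downside is that one planned exploratory moderator hypothesis is reclassified.

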## Methods/design

### Study design

This randomized control trial (RCT), will be conducted to address the specific aims of this research. African American parents (i.e., caregivers) newly diagnosed in the past 12 months of stages I, II, or III solid tumor cancer (e.g.., breast, lung, prostate, colon) and who have at a least one of their adolescent children (ranging in age 12–18 years old) living at home will be randomized to one of two five-session treatments. Families Fighting Cancer Together (FFCT) will include parent and adolescent child(ren) participation and Psychoeducation (PED) consists on psycho-education for the parent only. The University of Delaware Institutional Review Board and participating recruitment sites have approved all study protocols. A list of study sites can be obtained from clinicaltrials.gov. Participating parents in the study will provide informed consent and their adolescent child(ren) will offer written assent. A target sample of *N =* 172 families will be recruited over the 5-year study.

### Statistical power

Sample size was determined from pilot study data for the primary outcome (child depressive symptoms on the CDI) and endpoint (post-treatment) using power = 8 and α = .05 [27]. For all other analyses, minimum detectable effects are presented for fixed sample size. Pilot data indicate a greater decrease in depressive symptoms from pre-treatment to post-treatment among children in the FFCT intervention compared with children receiving PED equivalent to an effect size of Cohen’s d = 0.38, and pre-post correlations of 0.68. This suggests that a sample size of 60 families per study arm will yield power ≥ .8 with α = .05. Conservatively assuming retention of 70% (retention in the single site pilot was 85%), this indicates that recruitment of 172 study participants will ensure adequate statistical power for testing the primary study aim.

For tests of differences at post-treatment, a total sample size of 120 is used. Minimum detectable effects (in SD units) vary as a function of the correlation between pre-treatment and post-treatment measures and range between 0.31 for a correlation of 0.8 and 0.51 for a correlation of 0.2. Test of differences at 12-month follow-up assume that 80% of participants at post-treatment are retained to follow-up but benefit statistically from two additional occasions of measurement. Minimum detectable effects (in SD units) vary as a function of the correlation between pre-treatment and follow-up measures and range between 0.28 for a correlation of 0.8 and 0.38 for a correlation of 0.2.

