### Randomization

Randomized permuted blocks will be used to allocate groups of parent-adolescent dyads to each study arm (FFCT or PED). The data manager will prepare complete sets of allocations which will be placed in sequentially numbered sealed opaque envelopes containing treatment assignments for each group of 5 to 8 families. Once 5 families are recruited, group allocation will be made after a week has elapsed without any additional family participants recruited or once 8 families have been recruited, whichever occurs first.

The assessment team will be blind to the allocation condition and know only the serial numbers. At randomization, following baseline assessments, only the program manager opens the envelope for the group’s allocation. This approach provides both dynamic balancing and prospective partial blinding of the project manager to treatment assignment. At the end of the study, unused sealed envelopes will be retained along with the log to assure that randomization has been carried out as assigned.

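### The stated power of at least 0.8 with 60 families per arm holds only if families are randomised independently, but the trial randomises whole groups

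*Protocol article*

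**What the plan says.** The Statistical power section takes its inputs from the pilot: Cohen's "d = 0.38, and pre-post correlations of 0.68". From these it concludes: "This suggests that a sample size of 60 families per study arm will yield power" of at least .8 at α = .05. It then allows for 70% retention, which it calls conservative against 85% in the pilot, and states that "recruitment of 172 study participants will ensure adequate statistical power for testing the primary study aim". It also gives minimum detectable effects at post-treatment, for 120 families in total, of 0.31 SD (correlation 0.8) to 0.51 SD (correlation 0.2). It mentions no intracluster correlation, design effect or number of groups.

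The Randomization section describes a different unit of allocation. The sealed envelopes are described as "containing treatment assignments for each group of 5 to 8 families", and a group is allocated as a whole once enough families have been recruited. The Treatment Fidelity section expects 86 families per arm in 14 FFCT groups and 14 PED groups. The Analysis plan for Aim 1 is an ANCOVA of post-treatment CDI on baseline CDI and arm, with sandwich standard errors clustered on site and family.

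**The concern.** When intact groups are randomised, the outcomes of families in one group may be correlated, through shared sessions, shared facilitators or the same recruitment period. The variance of the treatment contrast is then inflated by a design effect, and the information about treatment comes from the number of groups, here about 28. A power figure computed for 120 independent families overstates what the trial can detect.

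The figure supports the primary aim. If it is too high, a null result on adolescent depressive symptoms would be read as coming from an 80% powered trial when the chance of missing the pilot effect was larger than 20%.

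**Working it through.** **Inputs from the article.** d = 0.38, r = 0.68, 60 analysed per arm, α = 0.05, 70% retention and 172 recruited (Statistical power); 14 groups and 86 families per arm (Treatment Fidelity). The target power is printed once as 8, an evident misprint for .8. Sidedness is not stated; two-sided is assumed, and two-sided ANCOVA is the variant that fits best.

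**1. Reproducing the stated figures, with independent families.**
- Residual SD = √(1 − 0.68²) = 0.733.
- SE = 0.733 × √(2/60) = 0.134; non-centrality = 0.38/0.134 = 2.84.
- Power from the non-central t on 117 df = **0.804**. The normal approximation gives 0.810 and requires 59 per arm.
- Recruitment: 120/0.7 = 171.4, hence **172**.
- Minimum detectable effects at 60 per arm, 117 df and design effect 1: **0.309** (r = 0.8) and **0.505** (r = 0.2), printed as 0.31 and 0.51.

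The alternatives fit less well: a two-sided change-score analysis gives 0.740 and a two-sided post-only comparison 0.548. The printed figures therefore contain no allowance for clustering.

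**2. Slack.** On 117 df the largest design effect that keeps power at 0.80 is 1.01. With 4.29 families per group this is an ICC of 0.01/3.29, about 0.003. With the normal approximation the limits are 60/58.4 = 1.03 and an ICC of about 0.008.

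**3. Power for the design used.** Retained families per group m = 60/14 = 4.29. Design effect DE = 1 + (m − 1) × ICC. SE = 0.733 × √(2 × DE/60). Group-level df = 28 − 2 = 26. The ICC is an assumption, on the baseline-adjusted scale; equal group sizes and one adolescent per family are also assumed.

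| ICC | DE | Power, 26 df | Power, 117 df |
|---|---|---|---|
| 0 | 1.000 | 0.780 | 0.804 |
| 0.01 | 1.033 | 0.767 | 0.791 |
| 0.02 | 1.066 | 0.754 | 0.779 |
| 0.05 | 1.164 | 0.717 | 0.742 |
| 0.10 | 1.329 | 0.660 | 0.685 |
| 0.15 | 1.493 | 0.609 | 0.635 |

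**4. More favourable cases.**
- Correlation in the FFCT arm only, SE = 0.733 × √((DE + 1)/60). At ICC 0.02, 0.05 and 0.10, power is 0.767, 0.748 and 0.717 on 26 df, or 0.791, 0.772 and 0.742 on 117 df.
- 85% retention, so 86 × 0.85 = 73 per arm and m of about 5.2, both arms correlated, 26 df: 0.825, 0.783 and 0.715 at the same ICCs.
- 85% retention and correlation in FFCT only, 26 df: 0.839, 0.818 and 0.782.

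**5. Minimum detectable effects.** At ICC 0.05, multiplying by √1.164 = 1.079 takes 0.309 and 0.505 to 0.33 and 0.55. Using 26 df as well gives 0.34 and 0.56.

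**The case against.** The article gives no ICC, so every loss beyond the df effect rests on an assumption. The 26 df are not the article's own test either: the Analysis plan describes an individual-level ANCOVA with standard errors clustered on site and family. If families were truly independent, 0.804 would stand. PED is a parent-only programme, so adolescents in that arm share no sessions, and correlation in adolescent CDI would arise mainly under FFCT. Finally, 70% retention is cautious: at 85%, power on 26 df stays at or above 0.80 up to an ICC of about 0.037 with both arms correlated, or about 0.075 with FFCT alone correlated.

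Much of this stands as a limit on the size of the shortfall. The ICC is unknown, and 172 recruited families could give adequate power if retention is good and the ICC is small. It does not rescue the stated figure. At 60 per arm, power is below 0.80 on 117 df from ICC 0.01 (0.791), and with correlation in FFCT only it is 0.797 at ICC 0.01. PED groups are also allocated as intact groups formed by recruitment time, so zero correlation there is not assured. The 85% case describes 73 per arm, whereas the claim is made for 60. Clustering the standard errors on site and family does not account for the randomised group, and no variance adjustment restores power that was not planned. Nor is this detail left to a fuller document: the printed 60, 172, 0.31 and 0.51 all reproduce with a design effect of exactly 1.

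**Conclusion.** The concern holds. The arithmetic is right for an individually randomised trial, which this is not. For 60 families per arm in about 28 randomised groups, power is about 0.77 to 0.66 over ICC 0.01 to 0.10 with group-level df, and about 0.79 to 0.69 if 117 df are kept. The direction does not depend on the df or on whether PED is correlated; the size depends on an ICC that the article does not give. At the pilot's 85% retention, 172 recruited families reach 0.80 only for small ICCs, so the unqualified assurance of adequate power is not supported either. The post-treatment minimum detectable effects are too small for the same reason.

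**What to change.** Restate the power paragraph for the design used: about 28 randomised groups, DE = 1 + (m − 1) × ICC with m of about 4.3 at 70% retention, and group-level df. Replace the single power claim with a table for ICC 0.01 to 0.10 at 70% and 85% retention, stating the basis for the ICC values and whether PED is taken as correlated. Multiply the post-treatment minimum detectable effects by √DE and compute them with group-level df. The restated power presumes a primary analysis that accounts for the randomised group, so the wording should be kept consistent with the Analysis plan, which now names only site and family.

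The cost is a rewording of the power section and a less favourable stated power, about 0.66 to 0.77 at 70% retention. No change to the sample size or to conduct is asked for.

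### The detectable effects given for 12 months (0.28 to 0.38 SD) belong to an average over three follow-up visits; a 12-month difference needs about 0.35 to 0.57 SD.

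*Protocol article*

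**What the plan says.** The Statistical power section of the protocol article gives two ranges of minimum detectable effect in SD units, each as a function of the correlation with the pre-treatment measure.

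- **Post-treatment.** "For tests of differences at post-treatment, a total sample size of 120 is used", and the detectable effects "range between 0.31 for a correlation of 0.8 and 0.51 for a correlation of 0.2".
- **12-month follow-up.** The tests "assume that 80% of participants at post-treatment are retained to follow-up" "but benefit statistically from two additional occasions of measurement". The detectable effects then "range between 0.28 for a correlation of 0.8 and 0.38 for a correlation of 0.2".

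The section does not say that the second range refers to anything other than a difference at 12 months. The longitudinal analysis under Exploratory aim 3a is a random coefficients model, and its evidence for benefit is a negative treatment difference in slope over time.

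**The concern.** The second range is smaller than the first at the same correlations, although it rests on fewer families. For a comparison at a single time point, losing a fifth of the sample can only raise the detectable effect. With no further loss at all, the 12-month values would equal the post-treatment ones, 0.31 to 0.51. Extra measurement occasions lower the detectable effect this much only if the effect is averaged over visits, or assumed to be the same at each of them. That is a different quantity from a 12-month difference.

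What is at stake is the reading of the follow-up results. Someone told that 0.28 to 0.38 SD is detectable at 12 months may take a null result as evidence that the benefit has faded, when the trial had roughly even odds, or somewhat better, of detecting an effect of that size.

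**Working it through.** **Inputs, all from the Statistical power section unless noted**

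- α = 0.05. Sidedness is not stated; two-sided is assumed.
- Power 0.80 ("will yield power ≥ .8 with α = .05").
- Post-treatment: "a sample size of 60 families per study arm", so n = 60 per arm.
- 12 months: 0.80 × 120 = 96, so n = 48 per arm.
- Post-baseline occasions: post-treatment plus two more = 3 (weeks 8, 24 and 52, from the Abstract and Table 1).
- Correlations 0.8 and 0.2. Equal correlation between all pairs of visits is assumed.

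**Formula**

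ANCOVA detectable effect = (1.960 + 0.842) × √(2V/n), in SD units. The small-sample version replaces the normal quantiles with the noncentral t distribution.

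- Single visit: V = 1 − r²
- Mean of k post-baseline visits: V = (1 + (k − 1)r)/k − r²

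**Step 1. Reproduce the post-treatment range (n = 60, single visit)**

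- r = 0.8: V = 0.36; 2.802 × √(2 × 0.36/60) = 0.307; t version 0.309. Printed: 0.31.
- r = 0.2: V = 0.96; 2.802 × √(2 × 0.96/60) = 0.501; t version 0.505. Printed: 0.51.

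**Step 2. Reproduce the 12-month range (n = 48, mean of three visits)**

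- r = 0.8: V = 2.6/3 − 0.64 = 0.2267; 2.802 × √(2 × 0.2267/48) = 0.272; t version 0.275. Printed: 0.28.
- r = 0.2: V = 1.4/3 − 0.04 = 0.4267; 2.802 × √(2 × 0.4267/48) = 0.374; t version 0.377. Printed: 0.38.

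One method therefore gives all four printed figures. The two-sided alternatives tried at n = 48 do not match both ends of the 12-month range (normal quantiles):

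| Quantity | r = 0.8 | r = 0.2 |
|---|---|---|
| Mean of two visits, ANCOVA | 0.29 | 0.43 |
| Mean of four visits, ANCOVA | 0.26 | 0.34 |
| Mean of three visits minus baseline | 0.30 | 0.59 |
| Mean of three visits, no baseline adjustment | 0.53 | 0.39 |

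**Step 3. Compute the quantity the text names (n = 48, week 52 only)**

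- r = 0.8: 2.802 × √(2 × 0.36/48) = 0.343; t version 0.347. Against 0.28 printed: 0.347/0.28 = 1.24.
- r = 0.2: 2.802 × √(2 × 0.96/48) = 0.560; t version 0.566. Against 0.38 printed: 0.566/0.38 = 1.49.

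Against the unrounded three-visit values the ratios are 1.26 and 1.50. At the pilot pre-post correlation of 0.68, the single-visit value is 0.424 against 0.329 for the three-visit mean, a ratio of 1.29.

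Power at week 52 for the printed effects (t version) is 62% for 0.28 at r = 0.8 and 47% for 0.38 at r = 0.2.

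**Step 4. Can the earlier visits rescue the 12-month contrast?**

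A repeated-measures model with a free week-52 effect, which also uses the 12 per arm seen at week 8 but lost afterwards, gives 0.336 and 0.559. That is almost no gain over 0.343 and 0.560.

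**Step 5. The Aim 3a slope test**

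With linear time at weeks 0, 8, 24 and 52 (mean 21, sum of squared deviations 441 + 169 + 9 + 961 = 1,580) and a free baseline difference between arms, the divergence projected to week 52 has V = (52²/1,580)(1 − r) = 1.711(1 − r).

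- r = 0.8: V = 0.342, giving 0.335 (t version 0.338).
- r = 0.2: V = 1.369, giving 0.669 (t version 0.676).

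If the arms are constrained to a common baseline, the values are 0.324 and 0.536. Both sets lie above the printed range.

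**The case against.** The strongest reply is that the text announces a repeated-measures gain and the numbers are correct for one, so this is an under-described quantity rather than a slip in calculation. That is partly right. The figures are valid for an effect that is constant over weeks 8, 24 and 52, and the fault lies in what they are attached to. But mentioning extra occasions only discloses an input. The labelled quantity is still a difference at 12 months, no constant-effect assumption is stated, and the printed sensitivity is wrong for that label.

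Other points have some force:

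- **The averaging formula is inferred.** The article does not name its model. The formula does use only the article's own inputs, and it reproduces both ends of the range.
- **The largest discrepancy occurs only at r = 0.2.** At the pilot correlation of 0.68 it is 29%. The correlation over 12 months may well be lower than over eight weeks.
- **The 12-month aims are exploratory.** No sample-size choice or decision rule depends on these figures. Under Exploratory aim 3c, the plan also intends to report interval half-widths, which would show the actual imprecision. This limits the harm but leaves the planning figure wrong.
- **The slope values depend on how baseline is modelled.** They do, but the equation under Exploratory aim 3a carries a treatment-specific intercept, which corresponds to the free-baseline values. The constrained version also exceeds the printed range.

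**Conclusion.** The concern holds. The stated 12-month detectable effects of 0.28 to 0.38 SD are those for the mean of three post-baseline visits. For a difference at 12 months with 96 families they should be about 0.35 (r = 0.8) to 0.57 (r = 0.2), which is 24% and 49% above the printed values. The printed effects have about 62% and 47% power at that visit. The Aim 3a slope test needs a divergence by week 52 of about 0.34 to 0.67 SD.

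These figures assume two-sided α of 0.05, 80% power, equal allocation, equal correlations between visits and independent families. Families are treated in groups, and any clustering by group would raise the values further.

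The primary analysis is not touched. With d = 0.38 and r = 0.68, 59 per arm are needed, which supports 60 per arm, and 120/0.70 gives 172.

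**What to change.** Correct the sentence in the Statistical power section in one of two ways:

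1. Keep the label and restate the 12-month minimum detectable effects as about 0.35 for a correlation of 0.8 and 0.57 for a correlation of 0.2.
2. Keep 0.28 to 0.38 and label it as the effect averaged over weeks 8, 24 and 52, assuming the effect is the same at each visit.

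The first is preferable, because it leaves the aims as they are. Under either option, give a separate figure for the slope test of Aim 3a, with its assumptions about baseline and linear time. Noting that the values take no account of treatment-group clustering would be a useful addition, but the correction does not depend on it.

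The cost is one or two sentences and a less favourable figure. Enrolment, conduct and the primary analysis do not change.
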